### Study population

The study will be carried out at the Primary Health Care System in urban areas. The study subjects will be adults both male and female living near two health centers in the city of Salamanca (La Alamedilla, Miguel Armijo), an estimated population of 42.000 residents. The health care professionals of both centers will offer the caregivers of dependent relatives the opportunity to participate on the study. Once the informed consent is signed, a researcher will complete the preintervention assessment by means of an individual interview.

The sample size is expected to reveal a difference of or superior to 12 units on the Ruiz-Baca's quality of life questionnaires between the intervention group and its control. With an estimated alpha risk 0.05 and a beta risk 0.20 in a bilateral contrast, 73 subjects are required in the first group and 73 in the second one. The common standard deviation assumed is 25.7 from a previous study.

Through consecutive sampling, 150 caregivers will be included, who are responsible for almost all the care given to dependent and ill relatives who receive health care in the centers. One half will be randomly assigned to the trial group and the other half to the control group in a waiting list format. Those in the control group will be offered to participate in the therapy sessions, but only once the intervention and final assessment of the first group have been completed. Those in the intervention group will be divided into groups of 8 and 12 subjects for the group sessions.

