### Statistical analysis

Data input will be made using the Teleform system (Autonomy Cardiff Vista, California, USA), with a questionnaire previously designed for the project, and exporting the data to the SPSS version 15.0 statistical package (SPSS Inc., Chicago, Illinois, USA) for posterior analysis.

A first descriptive analysis of the socio-demographic characteristics of the study groups will be made. The data will be presented with the mean and standard deviation in the case of quantitative variables, and as frequency distributions for qualitative variables. The Pearson chi-squared test will be used to analyze associations between qualitative variables. The Student t-test for independent samples will be used to compare the means for the two groups. In turn, the analysis of repeated measures will be based on the McNemar test for qualitative data and the Student t-test for paired data in application to quantitative data.

In order to describe the characteristics and intensity of the caregivers' analyzed variables, the sum of the grades as well as its mean will be used, so as to compare the range of grades and make their interpretation easier. Analyzing the impact of the intervention will be carried out through intent to treat analysis.

The contrasting hypothesis will establish an alpha risk factor of 0.05 as the limit of statistical significance.

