### Limitations

Although the simple size of the groups to be studied is quite large, taking into account the studies carried out so far in this type of interventions, it might be insufficient to accomplish definitive results. Due to the studied caregivers' greater accessibility to the health care center, the number of lost cases at the study completion is expected to be low, obtaining this way a somewhat larger simple than that of the studies performed in another context.

The intervention group and the control group will be both examined by the same assessors, who will not be responsible for the sessions. This should render an appropriate internal validity of the study.

The questionnaires used to know what the caregivers' situation is have proved not to be sensitive enough with regards to the changes affecting the caregivers. Changes might occur although caregivers are often satisfied with participating on the therapies. They nevertheless do not match the results obtained.

The greater limitation derives from the increasing tendency in specialized theoretical works indicating that the fact of not obtaining positive results with the interventions might be due to the fact that effectiveness is not assessed on a long-termed objective. The study will perform the final assessment six months after the first assessment.

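### Intention to treat is paired with an unadjusted t-test that ignores the baseline score; a baseline-adjusted comparison by randomised arm would protect against unequal loss and offset the thin 2.7% margin

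*Protocol article*

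**What the plan says.** All references are to the protocol article.

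- **Statistical analysis.** Two-group means are compared with Student's t-test for independent samples, and associations between qualitative variables with the chi-squared test. Repeated measures are analysed with the McNemar and paired t-tests. The section adds: "Analyzing the impact of the intervention will be carried out through intent to treat analysis". It does not say whether the two-sample test is applied to six-month scores or to change. The Abstract calls change in caregivers the principal measure.
- **Result Variables.** Outcomes are measured before the intervention and once more, six months after the first assessment. A baseline quality-of-life score is therefore collected before the intervention.
- **Organization of data collection.** Missing information is recovered where possible.
- **Study population.** The target is given as follows: "The sample size is expected to reveal a difference of or superior to 12 units on the Ruiz-Baca's quality of life questionnaires". For the spread, the section states: "The common standard deviation assumed is 25.7 from a previous study". The test is two-sided at 5% with 80% power, and the resulting requirement reads: "73 subjects are required in the first group and 73 in the second one". Recruitment is then set out: "Through consecutive sampling, 150 caregivers will be included". On allocation, the section says: "One half will be randomly assigned to the trial group and the other half to the control group in a waiting list format". No allowance for loss is stated.
- **Limitations.** Because of the caregivers' access to the health centre, "the number of lost cases at the study completion is expected to be low". The same section concedes that the sample might be insufficient for definitive results.

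**The concern.** The named two-sample test needs a six-month score, and the paired tests need a complete pair. Unless values are imputed, a caregiver without the six-month interview contributes nothing, although intention to treat is the stated principle. The test also leaves the baseline score unused, or uses it only through simple subtraction.

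The design gives some reason to think loss could differ by arm. Only the intervention arm is asked to attend eight 90-minute group sessions, while controls are offered the therapy once the final assessment is done. If the caregivers lost from the intervention arm tended to be those in the worse initial state, those remaining would look better at six months with no treatment effect at all. An unadjusted comparison cannot separate that from benefit.

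Precision is a second, smaller matter. Recruitment is only just above the calculated requirement, so even modest loss takes the unadjusted test below its planned power.

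**Working it through.** **Inputs.** From Study population: difference 12, SD 25.7, two-sided alpha 0.05, power 80%, 73 per arm required, 150 recruited in two halves (75 per arm). Assumed here, because the article gives no value: the loss rate, its dependence on baseline, and a baseline-to-six-month correlation r = 0.6.

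**1. The plan's own figure.** n per arm = 2 × (1.960 + 0.842)² × 25.7² / 12² = 72.001, rounded up to 73. The stated size reproduces.

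**2. Margin.** 75 − 73 = 2 per arm; (150 − 146)/150 = 2.7%.

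**3. Power of the unadjusted t-test with equal loss in both arms** (noncentral t, noncentrality 12 / (25.7 × √(2/n))):

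| Loss per arm | n per arm | Power |
|---|---|---|
| 0% | 75 | 81.1% |
| 2.7% | 73 | 80.0% |
| 5% | 71.25 | 79.0% |
| 10% | 67.5 | 76.8% |
| 15% | 63.75 | 74.4% |
| 20% | 60 | 71.8% |

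The decline is gradual: about one point below 80% at 5% loss, and about three at 10%.

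**4. Bias under no treatment effect, with loss in the intervention arm only.** The probability of loss is logistic in baseline score, with slope 1 per SD towards worse quality of life, and is calibrated to 10, 20 and 30% loss. Numerical integration puts the retained intervention caregivers' mean baseline about 0.091, 0.174 and 0.253 SD above that of controls. Call this shift s.

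- Bias on six-month scores = r × 25.7 × s.
- Bias on change scores = −(1 − r) × 25.7 × s.
- Standard error of the difference on six-month scores = 25.7 × √(1/75 + 1/n₁), with n₁ = 67.5, 60 and 52.5.
- Type I error = Φ(−1.96 + b) + Φ(−1.96 − b), where b is bias divided by standard error.

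| Loss, intervention arm only | Bias, six-month score | SE | Type I error | Bias, change score |
|---|---|---|---|---|
| 10% | +1.4 | 4.31 | 6% | −0.9 |
| 20% | +2.7 | 4.45 | 9% | −1.8 |
| 30% | +3.9 | 4.62 | 13% | −2.6 |

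A simulation of 4,000 trials per setting agrees with these values. On the same simulated data a baseline-adjusted model has bias within 0.1 unit and type I error of about 5%.

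**5. The same mechanism in both arms.** The shift s is then equal in the two arms and cancels. Type I error stays at about 5%.

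**6. What baseline adjustment does for power.** At r = 0.6 the residual SD is 25.7 × √(1 − 0.36) = 20.56. With 60 per arm the standard error is 20.56 × √(2/60) = 3.75, and 12/3.75 = 3.20, so power is Φ(3.20 − 1.96), about 89%. The correlation needed to restore the planned precision satisfies 1 − r² = n/73. At 20% loss r = √(1 − 60/73) = 0.42; at 10% loss r = √(1 − 67.5/73) = 0.27.

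**The case against.** Several counter-arguments have force.

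- **The text does not restrict the analysis to completers.** A reader might infer that the article contradicts its own intention-to-treat claim. It does not. A t-test is compatible with analysis by randomised arm and with imputed values. An article may also leave the handling of missing outcomes to the full protocol or analysis plan, so that silence alone is no finding. What stands is the choice the article does make: an unadjusted test where a baseline score is available.
- **Unequal, baseline-related loss is assumed.** The article gives no rate, expects few losses and offers a reason. Assessors who do not run the sessions examine both arms, so the outcome interview is separate from attendance. Waiting-list controls could be lost too, and similar loss in both arms produces no inflation. This limits the bias figures to an illustration of what could happen.
- **The direction of bias depends on an unstated choice.** On six-month scores it favours the intervention; on change scores it goes against it and is smaller. This stands, and it is a further reason to prefer the adjusted analysis, which is close to unbiased under the mechanism examined.
- **The power table and the bias table use different loss patterns**, equal in the first and one-sided in the second. They should not be read together. With about 10% loss in the intervention arm alone, power is about 79% rather than 77%.

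**Conclusion.** The point holds as a weakness in the chosen primary comparison. The named test omits caregivers without a six-month score by default and makes poor use of the baseline score. Under one-sided, baseline-related loss of 10 to 30% at r = 0.6, it would have a type I error of about 6 to 13% on six-month scores. All of those conditions are assumptions. With similar loss in both arms there is no inflation.

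A reader might also infer from the 2.7% margin that the stated 80% power collapses as soon as caregivers are lost. The figures do not support that. Power is still 80.0% with 2 lost per arm and 79.0% at 5% loss; it reaches about 77% at 10% and 72% at 20%. A material shortfall needs a loss rate that the article does not give and does not expect. Baseline adjustment would more than make up for it if the correlation is near 0.6.

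**What to change.** 1. Make the primary between-arm analysis a baseline-adjusted comparison of six-month quality of life by randomised arm. Use either a likelihood-based model for the baseline and six-month scores with baseline means constrained equal, or multiple imputation including baseline score and centre. All 150 randomised caregivers then contribute, which gives the intention-to-treat statement a definite meaning. Keep the within-arm paired and McNemar tests as description only. Either method assumes that loss depends only on what has been observed; state that assumption.
2. Beside the sample size, note that 150 covers 2 losses per arm (2.7%) for the unadjusted test, whose power would be about 77% at an assumed 10% equal loss and 72% at 20%. Add that baseline adjustment would recover this if the correlation is near 0.6.

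The cost is a little analysis work and two or three sentences of text. The baseline score is already collected, and no extra enrolment is needed.

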### Ethical and legal issues

In order to guarantee data confidentiality, all the electronic and paper copies of the protocol, signed informed consent documents and results of the tests made in each of the patients will be kept locked in a safe place, and only the study investigators will have access to the data on the subjects who agree to participate in the study.

The protocol was approved (April 25, 2008) by the Research ethics committee from University hospital of Salamanca, Spain and complies with Spanish data protection law 15/1999 and its recently developed specifications (Royal Decree (RD) 1720/2007). Knowledge and agreement to cooperate has been established with the implicated services, signed by the legal representative of the centre.

### Limitations

Although the simple size of the groups to be studied is quite large, taking into account the studies carried out so far in this type of interventions, it might be insufficient to accomplish definitive results. Due to the studied caregivers' greater accessibility to the health care center, the number of lost cases at the study completion is expected to be low, obtaining this way a somewhat larger simple than that of the studies performed in another context.

The intervention group and the control group will be both examined by the same assessors, who will not be responsible for the sessions. This should render an appropriate internal validity of the study.

The questionnaires used to know what the caregivers' situation is have proved not to be sensitive enough with regards to the changes affecting the caregivers. Changes might occur although caregivers are often satisfied with participating on the therapies. They nevertheless do not match the results obtained.

The greater limitation derives from the increasing tendency in specialized theoretical works indicating that the fact of not obtaining positive results with the interventions might be due to the fact that effectiveness is not assessed on a long-termed objective. The study will perform the final assessment six months after the first assessment.

## Discussion

Publications relating to interventions designed to improve the caregivers' mental health are scarce. Moreover, most of them focus on caregivers of patients suffering from dementia. Some of the publications are characterized by important methodological limitations to establish comparisons among different interventions [1-3,22]. It is important to describe which content and procedures are used in an intervention program and how they are implemented. Taking into account the premise that not everything is equally valid, it is necessary to consider certain variables (such as the time dedicated to the learning of each capacity and strategy used) to measure the effectiveness, which should be performed considering the content and objectives used in the intervention [23,24].

It has been demonstrated that all psychotherapeutic interventions are not effective when reducing the caregiver's discomfort. Psychotherapeutic interventions obtain best results in reducing the symptomatolgy and improving the emotional state of the caregivers. Individual therapies offer better results than group therapies [7].

The significance of our study comes from the fact that it will apply on caregivers of patients familiar with dementia a project proven to be effective in a different context than that of the Primary Health Care System and developed by mental health professionals. If it proves to be effective both with caregivers of patients with and without dementia and with Primary Health Care professionals, it would be an important instrument to be offered to dependent patients.

The content of the intervention sessions, the documents to be completed by caregivers, and the test to be assessed will be applied equally by two professionals in both health care centers. The aim is to assess the reproducibility of such material and determine if the intervention is effective, the possibility to reproduce it in different primary health care centers. If so, it could be subsequently be introduced in general care programs.

Finally, if the results of the intervention are positive, it will be important to know if they persist in time. This would enable the establishment among other things of the financial resources that should be destined to these therapies and compared with other alternatives offered to the relatives who take care of the dependent patients.
